## Study design and methods

### Study design

This is a single-center randomized controlled trial, and participants will be assigned to receive acupuncture or sham acupuncture in a 1:1 ratio. Each participant will sign an informed consent form prior to enrollment. The protocol followed SPIRIT for TCM statement (22).

The total observation period will be 12 weeks, including an 8-week intervention period (weeks 0-8), and a 4-week follow-up period (weeks 8-12). Assessments will be conducted at baseline, week 2, week 4, week 6, week 8 and week 12. The study process is illustrated in **Figure 1**, while the schedule of enrolment, treatments, and assessments can be seen in **Table 1**.

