### Primary outcome

Difference in CDRS-R scores at weeks 0 and 8 of treatment.

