### Statistical considerations

#### Sample size

This trial is a pilot trial aim to preliminarily explore the possibility of acupuncture in the treatment of ADD, and to evaluate the feasibility of conducting further large-scale clinical trials to verify the efficacy of acupuncture. Moreover, the results of this trial will facilitate the calculation of an appropriate sample size for further randomized clinical trials. The minimum sample size for exploratory trials is 20 to 30 per group according to Provisions for Drug Registration in China. It is generally accepted that at least 30 participants are required for a pilot study (24). According to an estimate of the number of patients expected to participate in the trial and the minimum number of patients required to assess the practical purpose of the trial., we choose the maximum of 30 participants, and the sample size of 60 participants is determined.

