### Statistical analysis

The primary and secondary outcomes of this study will be analyzed using the modified intention to score principle. The other statistical analyses including feasibility outcomes and security outcomes. And the safety analysis will include all patients who have received at least one time of intervention.

Analyses of the primary outcomes will be conducted using linear mixed-effects models (MMRM) and generalized linear mixed models (GLMM) in repeated-measures design, which incorporate the clinical effect rates at weeks 0, 2, 4, 6, 8, and the follow-up period as response variables, as well as baseline values, time with treatment factors, time, and treatment factors as fixed-effects variables for the analyses. This study will assume that missing indicators are randomized, and due to the ability of the MMRM to cope with randomly missing data, this study will not conduct data filling for the primary outcome.

Reliability of our data will be analyzed using Cronbach’s Alpha, which is a commonly used indicator for assessing the internal consistency of a scale (25), and data assessed through the scale are considered reliable only when it is >0.7.

Three sensitivity analyses will be conducted in this study for the primary outcomes. First, the study will exclude missing data and analyzes the complete case dataset. Second, a multiple filling method will be used to fill in the outcomes before conducting the evaluation. Third, the primary outcome will be analyzed based on the set of compliant scenarios. In addition, the study will also conduct subgroup analyses of the primary outcome, which will include gender, age, hospital district, BMI, duration of disease, comorbidities, and medication use. For the analysis of secondary outcome, repeated measures information will also be based on the MMRM method; for other quantitative data outcomes, this study will use the Mann-Whitney U test or t-test, depending on whether the data are normally distributed or not.

Statistical descriptions will be carried out for the adverse reaction indicators, and the method of chi-square test or Fisher’s exact probability will be used to compare the differences between groups.

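### Week 0 is both a response and, through the baseline covariate, a predictor in the primary repeated-measures model, so the model as written is degenerate or misstates the precision of the week-8 group difference

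*Protocol article*

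**What the plan says.** The primary outcome (Primary outcome section) is "Difference in CDRS-R scores at weeks 0 and 8 of treatment". For its analysis, the Statistical analysis section says: "Analyses of the primary outcomes will be conducted using linear mixed-effects models (MMRM) and generalized linear mixed models (GLMM) in repeated-measures design". The models are ones "which incorporate the clinical effect rates at weeks 0, 2, 4, 6, 8, and the follow-up period as response variables", and the fixed effects follow in the same sentence: "as well as baseline values, time with treatment factors, time, and treatment factors as fixed-effects variables for the analyses".

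The Study design section makes baseline the first of the scheduled visits: "Assessments will be conducted at baseline, week 2, week 4, week 6, week 8 and week 12". Table 1 heads that column as week 0. No other baseline measurement of CDRS-R is described. The article does not say that week-0 rows are left out of the fit, or that the groups share a common week-0 mean. Secondary repeated measures are to be analysed by the same method.

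**The concern.** A baseline-adjusted repeated-measures model uses the baseline value in one of two ways: as a covariate for the later visits, or as the first response. The article specifies both. At week 0 the covariate then equals the response, and that row carries no residual information.

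This model carries the main between-group comparison. The article sets a test level of 0.05 and labels only secondary and subgroup results exploratory. It also relies on this model, without imputation, to handle missing data, and it says that the results will help size the next trial. A fit that fails would have to be replaced after the data are in. A fit that runs with a distorted residual variance could pass unnoticed.

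**Working it through.** **Inputs from the article.** Sixty participants ("the sample size of 60 participants is determined"), allocated 1:1, so 30 per arm; six visits including week 0; fixed effects for baseline, time, treatment and treatment by time. The article gives no SD, standard error or power for this model, so there is no figure to reproduce.

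**Assumptions.** SD 10 at week 0; later SDs 1, 1.3 or 1.5 times that; compound-symmetric correlation 0.3, 0.5 or 0.7, or AR(1) with 0.8 or 0.9 per two weeks; complete data; no true effect; z-test at 1.96; 1,500 simulated trials per scenario (Monte Carlo error of a rejection rate about 0.006).

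**Model as written.** Y_ij = m_j + d_j T_i + b B_i + e_ij, for j = 0, 2, 4, 6, 8, 12, with B_i = Y_i0.

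**1. Unstructured covariance.** Set b = 1, m_0 = 0 and d_0 = 0. Every week-0 residual is then exactly zero. The week-0 variance has no lower bound, and its term in the log-likelihood, -(n/2) log(variance), grows without limit. On one simulated dataset, iterative fitting gave:

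| Iteration | Baseline slope | Week-0 residual SD | Log-likelihood part |
|---|---|---|---|
| 0 | 0.570 | 3.84 | -660 |
| 3 | 0.966 | 0.305 | -508 |
| 10 | 0.9999 | 0.0008 | -153 |
| 40 | 1.0000 | 6e-13 | 1100 |

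The covariance matrix then became singular. With a separate baseline slope per visit it was numerically singular at the first step.

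**2. If software stops near that boundary.** The common slope is about 1 at every visit, so the week-8 estimate is a change-score difference. With equal SDs its variance is proportional to 2(1 - r), against 1 - r^2 for baseline adjustment. The ratio is 2/(1 + r): 2/1.3 = 1.54, 2/1.5 = 1.33 and 2/1.7 = 1.18 at r = 0.3, 0.5 and 0.7.

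**3. Random intercept (REML), week-8 group difference.** Each cell gives mean model SE / empirical SD = ratio; rejection rate.

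| Data | As written | Week-0 rows removed |
|---|---|---|
| CS 0.3 | 2.35/2.53 = 0.93; 0.070 | 2.46/2.52 = 0.98; 0.057 |
| CS 0.5 | 2.10/2.27 = 0.92; 0.077 | 2.24/2.27 = 0.99; 0.058 |
| CS 0.7 | 1.71/1.83 = 0.93; 0.076 | 1.85/1.83 = 1.01; 0.051 |
| CS 0.5, later SD x1.3 | 2.68/2.94 = 0.91; 0.082 | 2.92/2.95 = 0.99; 0.061 |
| CS 0.5, later SD x1.5 | 3.08/3.33 = 0.93; 0.069 | 3.36/3.33 = 1.01; 0.049 |
| AR(1) 0.8 | 2.07/2.43 = 0.85; 0.100 | 2.21/2.41 = 0.92; 0.075 |
| AR(1) 0.9 | 1.65/2.04 = 0.81; 0.121 | 1.78/2.03 = 0.88; 0.095 |
| AR(1) 0.9, later SD x1.3 | 2.12/2.64 = 0.80; 0.118 | 2.32/2.64 = 0.88; 0.082 |

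The empirical SD hardly differs between the columns; the reported SE does. The as-written SE is smaller than the SE without week-0 rows by 4.5% (2.35/2.46) to 8.6% (2.12/2.32). A second set of 1,500 trials per scenario, at unit SD and compound symmetry 0.3, 0.5 and 0.7, gave SE/SD of 0.235/0.247, 0.210/0.233 and 0.171/0.182. These are shortfalls of 5%, 10% and 6%. Rejection was 6.5%, 7.6% and 7.2%, against 4.7%, 5.6% and 4.9% without week 0.

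**4. Treatment by (week 8 minus week 0) contrast, same model.** SE/SD is 0.99 to 1.10 under compound symmetry and 0.81 to 0.85 under AR(1). With equal SDs its empirical SD is 3.08, 2.58 and 2.00, against 2.52, 2.27 and 1.83 for the baseline-adjusted difference. That is 22%, 14% and 9% larger, in line with step 2.

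**5. If the response is not the score.** The analysis sentence speaks of "clinical effect rates at weeks 0, 2, 4, 6, 8". The HAMD-17 reduction rate at week 0 is (pre - pre)/pre = 0 for everyone. Remission needs a score below 7 while entry needs at least 8, so nobody is in remission at week 0. A week-0 row is then a constant.

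**The case against.** **The primary outcome is a change.** The matching contrast is treatment by (week 8 minus week 0), whose SE is about right under compound symmetry. This stands, and it limits the claim of a too-small SE to the week-8 group difference. It does not rescue the model: the contrast gives up precision, and it is still undefined under an unstructured covariance.

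**Larger figures are tempting.** From the AR(1) rows a reader might infer that week 0 costs 15-20% of the SE and pushes the type I error to 10-12%. That is not supported: 8-12% of shortfall remains without week 0, because a random intercept is the wrong covariance for those data. A t reference also trims the excess. With 57 degrees of freedom (an assumption), a further run under compound symmetry gave 5.9-6.2%, against 6.4-7.2% by z.

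**Both consequences rest on an unstated covariance.** True. Leaving that structure to a fuller document is no fault of the article, and a failed fit would be visible to the analyst. A reader might infer that the primary result is bound to be invalid or anti-conservative; the article does not settle that. The fault lies in what it does state, the response visits and the fixed effects together.

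**The baseline term might mean other characteristics.** Many are listed under Observational indicators and follow-up, and that reading would remove the duplication. The sentence does not say so, and the baseline value of the outcome is the more natural reading.

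**This is a pilot.** There is no power calculation, and the stated progression thresholds concern completion and drop-out, not a p-value. That limits the damage, but it is no reason to keep a specification that cannot be fitted as intended.

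**Conclusion.** The point holds in a limited form. On the natural reading, the week-0 measurement is both response and covariate in the primary model.

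- **Unstructured covariance:** there is no valid maximum. The fit fails or becomes a change-score comparison, whose variance is 54%, 33% or 18% higher than with baseline adjustment at correlation 0.3, 0.5 or 0.7 (equal SDs).
- **Random intercept:** the week-0 rows make the SE of the week-8 group difference about 5-10% too small. The z-test type I error is about 7-8%, against 5-6% without them, under assumed compound symmetry of 0.3-0.7.
- **Change-from-week-0 contrast:** the SE is roughly correct under compound symmetry, but the contrast is less precise than the baseline-adjusted week-8 difference.
- **Response read as a change or rate:** its week-0 value is constant or undefined, so week 0 still cannot be a response row, although the simulated sizes above do not apply.

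The correlations and SDs are assumptions. The first two outcomes are alternatives, and the article does not determine which occurs.

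**What to change.** Choose one of two specifications and state it:

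1. Responses are CDRS-R at weeks 2, 4, 6, 8 and 12. Week-0 CDRS-R is a covariate, preferably with a baseline-by-visit term. The primary contrast is the group difference at week 8.
2. Week 0 stays among the responses, with a common baseline mean for the two groups and no baseline covariate.

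The two are similar but not identical: the second also keeps participants who have a baseline value only. They should not be combined. The covariance structure should be named with the model, the response should be called the CDRS-R score, and the same rule should apply to the secondary repeated measures.

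The cost is one phrase in the analysis text, with no change to visits, data collection or sample size. It should be settled before unblinded data are analysed.

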### Removal criteria

Participants who meet any of the following criteria will be removed: (1) Receive a treatment prohibited for this trial; (2) Poor compliance, not completing case observation forms, examinations or treatment as required after inclusion.

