### Discontinuation criteria

The trial leader will obtain these interim results and make the final decision to terminate the trial if the following occurs: (1) Participants suffer a severe illness or adverse reaction during the trial; (2) Participants request to discontinue the trial; (3) Participants suffer self-injury, suicidal behavior, or have a change in diagnosis and treatment due to medical condition changes during the trial; (4) Contrary to the purpose and protocol of the study.

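### None of the three planned sensitivity analyses, as worded, departs from the missing-at-random assumption of the primary model, so their agreement would not show robustness to informative withdrawal

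*Protocol article*

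**What the plan says.** Under Statistical analysis, the article sets the assumption for the primary model: "This study will assume that missing indicators are randomized". It gives this as the reason for not imputing: "due to the ability of the MMRM to cope with randomly missing data, this study will not conduct data filling for the primary outcome". It then fixes a counted list: "Three sensitivity analyses will be conducted in this study for the primary outcomes". The list has these entries:

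- A complete-case analysis, which leaves out participants with missing values.
- Multiple imputation, described in one sentence: "Second, a multiple filling method will be used to fill in the outcomes before conducting the evaluation".
- A repeat of the primary analysis in the compliant set.

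No delta-adjusted, tipping-point, reference-based or pattern-mixture analysis appears anywhere in the article.

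Other sections describe ways in which data may be lost:

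- **Removal criteria:** one ground is "Receive a treatment prohibited for this trial"; another is poor compliance.
- **Discontinuation criteria:** one item begins "Participants suffer self-injury, suicidal behavior, or have a change in diagnosis and treatment".
- **Data management and quality control:** questionnaires with blanks or patterned answers do not count as valid.
- **Feasibility outcomes:** drop-out of up to 20% still leads to a decision to proceed; 20% to 50% leads to modification.

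**The concern.** A sensitivity analysis for missing data is useful when it changes the assumption that cannot be checked from the observed data. Here that assumption is that, given baseline, arm and the earlier visits, those with no week-8 score would have done as the model predicts. Someone who leaves because their condition worsened after the last visit, or who starts another treatment, may not fit that.

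If the listed analyses all leave the assumption in place or tighten it, close agreement could be read as reassurance that it does not give. The Sample size section says the results will help to size a later trial, so the effect estimate will be used beyond this pilot.

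**Working it through.** **Step 1. What each analysis assumes about unseen week-8 scores.**

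| Analysis | Assumption | Relaxes missing at random? |
|---|---|---|
| Primary MMRM | Missing at random given baseline, arm and earlier visits | – |
| Complete cases | Generally stronger, because the week 2, 4 and 6 scores of those who leave are discarded | No |
| Multiple imputation | None stated; the usual default is the same as the MMRM | Not as worded |
| Compliant set | Selects on behaviour after randomisation, so the population changes | No |

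**Step 2. Size of a bias.** The article gives no effect size, SD or expected drop-out, so there is no figure to reproduce. Code the score so that lower is better. Let p be the share missing in an arm, and δ the average amount by which the unseen scores are worse than the model predicts. Then, approximately:

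reported difference − true difference = −(p × δ) in the acupuncture arm + (p × δ) in the sham arm.

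Take p = 0.20 in the acupuncture arm (6 of 30) and no departure in the sham arm. The 20% is the feasibility limit, applied here to one arm as an assumption; the shifts are also assumed.

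- δ = 0.25 SD: 0.20 × 0.25 = 0.05 SD
- δ = 0.5 SD: 0.20 × 0.5 = 0.10 SD
- δ = 1.0 SD: 0.20 × 1.0 = 0.20 SD

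These favour acupuncture. If the sham arm loses the poor responders, the sign reverses.

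**Step 3. Comparison with sampling error.** With 30 × 0.8 = 24 completers per arm and an assumed baseline–outcome correlation of 0.5:

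SE = √(2/24) × √(1 − 0.5²) = 0.289 × 0.866 = 0.25 SD.

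The three shifts are 0.05/0.25 = 0.2, 0.10/0.25 = 0.4 and 0.20/0.25 = 0.8 of one standard error.

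**Step 4. Simulation, for illustration.** 30 per arm, true effect 0, unit SD, correlation 0.6 between adjacent visits and decaying with distance, 20% missing at week 8 in each arm, 4,000 runs per mechanism. Sham losses are random. Acupuncture losses are random, or more likely with a worse week-6 score (missing at random), or more likely with a worse week-8 score (not at random). Only the 30 per arm and the 20% come from the article. A regression fit under missing at random stands in for the MMRM. The last column adds an assumed 0.8 SD to the predicted scores of acupuncture leavers. Negative values favour acupuncture.

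| Acupuncture-arm loss | Complete case | Missing-at-random model | Missing-at-random imputation | Shift of +0.8 SD |
|---|---|---|---|---|
| Random | 0.002 | 0.002 | 0.002 | 0.161 |
| Depends on week 6 | −0.138 | 0.004 | 0.005 | 0.164 |
| Depends on week 8 | −0.229 | −0.154 | −0.154 | 0.006 |

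Two things follow. Imputation under missing at random repeats the model's answer, including its bias (−0.154 and −0.154). Complete case does move away from the model, but the gap is larger when the model is right (−0.138 − 0.004 = −0.142) than when it is biased (−0.229 + 0.154 = −0.075). The gap cannot tell the two situations apart.

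The last column is no proof that 0.8 is the right shift. It moves the estimate by 0.20 × 0.8 = 0.16, as the formula in step 2 says, and reaches zero in the last row because the value suits that scenario.

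**The case against.** The strongest reply is that the imputation model is not stated. The article says only that "a multiple filling method will be used to fill in the outcomes before conducting the evaluation". Multiple imputation is also the vehicle for delta-adjusted and reference-based analyses, and a full protocol or SAP that is not shown could specify one. This stands in part: the documents do not show that the imputation will be run under missing at random. The point here is limited to the counted list as worded, which names no departure.

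Several stronger readings are tempting, and the documents do not support them.

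- A reader might infer that all the analyses share one bias and would give no warning. Step 4 shows otherwise: complete case gave −0.23 against −0.15. It is a partial and ambiguous signal, but not the same bias.
- A reader might infer that the effect would be overstated by 1/(1 − d), where d is the share lost: 1.25 times at 20% loss and 2.0 times at 50%. That arithmetic assumes that acupuncture participants who leave take on sham-like outcomes. It compares an effect while treated with an effect regardless of stopping, and the article does not fix the second as its target. Showing that reference-based imputation recovers the latter value is circular, because the data would be generated under its own assumption.
- A reader might infer that the bias must favour acupuncture. Nothing in the article says which arm will lose poor responders.
- A reader might infer that every listed exit ends data collection. The removal and discontinuation criteria do not say that assessment stops, and the discontinuation list is introduced as grounds for ending the trial. CDRS-R is also measured at weeks 2, 4 and 6, so worsening seen before an exit enters the MMRM and makes missing at random more credible.

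It is also fair to say that the article never claims that these analyses test informative withdrawal, and that a 60-person pilot has more sampling error than bias of this size. Both limit the weight of the point. Neither makes the list a check of the assumption on which the primary analysis rests.

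**Conclusion.** The concern holds in a limited form. The article states a missing-at-random assumption and lists exactly three sensitivity analyses, and as worded none departs from it. Their agreement with the MMRM would not show that the result withstands informative withdrawal, which is plausible given the listed exits and the drop-out the plan accepts.

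The size is unknown. On the assumptions in steps 2 and 3 it is 0.05 to 0.20 SD at 20% loss in one arm, in either direction, against a standard error of about 0.25 SD. This is a cheap improvement worth making before the data are seen. It is not an error that invalidates the primary analysis.

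**What to change.** 1. Keep the MMRM as the primary analysis.
2. Run the second sensitivity analysis, multiple imputation of week-8 CDRS-R, with a delta adjustment applied separately by arm over a range stated in advance. Include zero shift as the missing-at-random reference, and report the shift at which the conclusion would change (tipping point). Reference-based imputation from the sham arm can be added as an option, with its assumption stated.
3. Describe the complete-case and compliant-set results as supplementary, not as checks of the missing-data assumption.
4. Tabulate withdrawals and missing week-8 scores by arm and reason, so that readers can judge which shifts are credible.

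The cost is a short change of wording and a few lines of R within an imputation already planned. No new data or participants are needed. The downside is a sensitivity result that may look less favourable.

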### Randomization and blinding

In this study, participants will be divided into an intervention group and a control group using a block randomization method. The randomization sequence will be generated by a randomizer not involved in trial implementation and statistics with the aid of Stata software, setting a block length of 4, with the 60 participants divided into a total of 10 blocks.

The random assignment sequence and grouping results of the Stata software output will be recorded by the randomizer on paper and sealed in an opaque envelope with a number representing the order in which the participants are grouped. Envelopes will be kept by randomizer.

After the participants meet the enrollment criteria, sign the informed consent and complete the baseline data collection, the researchers will ask for a random number according to the enrollment order of the participants from randomizer, and then conduct clinical studies according to the predetermined treatment plan of each group.

Participating researchers include randomizers, therapists, assessors and statistical analysts. The study will be blinded to patients, assessors and statistical analysts. If a participant experiences a serious adverse reaction during the trial, unblinding will take place immediately. The procedure for unblinding will be the intervener explains to the trial leader the occurrence of a serious adverse reaction in the participant and requests unblinding. Data from this study will be reviewed and evaluated by the data monitoring committee (DMC), which consisted of 5–6 clinicians and statisticians independent of the sponsor and competing interests. And every three months there will be a trial monitoring by an independent clinical trial monitor.

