### Security outcomes

The outcomes of safety evaluation will be recorded, including basic vital signs (blood pressure, respiration, pulse, etc.) before and after treatment, and records of adverse events (AEs) during treatment and follow-up.

Classification of AEs: Serious Adverse Events (SAEs) are adverse medical events such as death, life-threatening, permanent or severe disability or loss of function, subjects requiring hospitalization or prolonged hospitalization, and congenital anomalies or birth defects that occur in the course of a clinical trial. Significant adverse events are defined as any occurrence of AEs other than SAEs that result in the use of targeted medical measures (e.g., cessation of needling, symptomatic treatment) and significant abnormalities in hematology or other laboratory tests. An unintended adverse event (UAE) is an AE that is of a different nature, severity, or frequency than the expected risk described in a previous protocol or other relevant information (e.g., investigator’s brochure, drug insert).

Handling of AEs: When a participant has trial-related AEs, including clinically significant abnormalities in laboratory tests, the participant should be assured of appropriate medical treatment, such as stopping the needling, decreasing the frequency, or symptomatic treatment. At the same time, to avoid more serious consequences of the clinical trial, the researcher should decide whether to terminate or suspend the clinical trial in order to protect the rights and safety of the participants.

Recording of AEs: Medical documents related to AE, including request forms for laboratory tests and report forms for test results, should be kept in the original files, and the original records should be kept true, accurate, and complete. All records should be signed and dated by the researcher. The content of AE record includes the name of the AE described in medical terminology, clinical signs/symptoms, start and end time of occurrence, severity, measures taken, and the outcome, etc., and the relevance to the trial protocol should be judged. Measures taken mainly include: no measures taken, adjustment of trial parameters, cessation of needling, combination of medications, hospitalization, or prolongation of hospitalization, etc. AE outcomes are mainly cured, improved, not cured, worsened, died, lost to visit, or unknown.

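### The only stated between-arm safety analysis covers undefined adverse reactions, although the safety outcome is defined as all adverse events

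*Protocol article*

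**What the plan says.** The Security outcomes section lists vital signs before and after treatment and "records of adverse events (AEs) during treatment and follow-up". It sets no relatedness condition on what is recorded. Each AE record must also carry a causality assessment: "the relevance to the trial protocol should be judged". On who completes the records it says only "All records should be signed and dated by the researcher".

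The Statistical analysis section says that security outcomes will be analysed and that everyone who received at least one session is included. The one sentence that gives a method opens with "Statistical descriptions will be carried out for the adverse reaction indicators". For the test between arms, the same sentence adds that "the method of chi-square test or Fisher’s exact probability will be used to compare the differences between groups".

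On roles, Randomization and blinding states "Participating researchers include randomizers, therapists, assessors and statistical analysts" and then "The study will be blinded to patients, assessors and statistical analysts". Therapists are in the first list and not in the second.

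**The concern.** What is collected and what is compared are named differently. In ordinary safety usage an adverse event is anything untoward that happens, and an adverse reaction is an event thought to be caused by treatment. Read that way, the planned test covers only a causality-filtered part of the defined outcome, and no stated method covers all AEs or all SAEs.

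Two things would be at stake.

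- **Bias from attribution.** Comparing all events between randomised arms needs no causality judgement. Comparing related events does. If the person judging knows the arm, the same event may be accepted as related after a penetrating needle and dismissed after a flat-tip one.
- **Loss of the events that matter most here.** In depressed adolescents, worsening mood or self-harm may be put down to the illness, judged unrelated, and so left out of the comparison.

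**Working it through.** **Step 1: the wording.** The plan states no safety figure, so there is nothing to reproduce. The question is what the analysis sentence covers.

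- Security outcomes uses *adverse event* throughout and separately mentions trial-related AEs. It never uses *adverse reaction* as a class of event.
- Background uses *adverse reactions* for effects that SSRIs may cause, which is a causal sense.
- Discontinuation criteria lists adverse reactions in item (1) and self-injury and suicidal behaviour in item (3), which suggests a narrower sense.
- Randomization and blinding speaks of a serious adverse reaction where Security outcomes has the category SAE, which suggests loose use.

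The term is therefore ambiguous, with some lean towards the narrower sense. An analyst could build either table from the sentence.

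**Step 2: whether the choice matters.** Inputs from the protocol: 60 participants at 1:1, so 30 per arm; Fisher's exact test; α = 0.05 (taken as two-sided, since sidedness is not stated). Assumed inputs, because the protocol gives none: a true AE risk r equal in both arms, at 20%, 30% or 40%; and the probability that an AE is called related, q₁ in the real arm and q₀ in the sham arm. For simplicity, each participant has at most one event.

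The proportions compared are p₁ = r × q₁ and p₀ = r × q₀. The false-positive rate is the sum, over all pairs (a, b) with a, b = 0…30 and Fisher p ≤ 0.05, of Bin(a; 30, p₁) × Bin(b; 30, p₀). For example, with r = 30%, q₁ = 80% and q₀ = 20%, p₁ = 0.30 × 0.80 = 0.24 and p₀ = 0.30 × 0.20 = 0.06, which gives 34.3%.

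| Events compared | r = 20% | r = 30% | r = 40% |
|---|---|---|---|
| All AEs | 2.2% | 2.6% | 2.6% |
| Related only, 50% v 50% | 0.9% | 1.7% | 2.2% |
| Related only, 80% v 50% | 3.9% | 7.8% | 11.9% |
| Related only, 80% v 20% | 14.6% | 34.3% | 54.0% |

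The excess depends on unequal attribution. With equal attribution the related-only test stays below 5%, as the all-AE test does.

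**Step 3: whether other outcomes close the gap.** Secondary outcomes compares CDRS-R, HAMD-17 and C-SSRS scores at weeks 0, 2, 4, 6, 8 and 12, so worsening and suicidality are also analysed there. However, these are scores at scheduled visits. Self-injury, suicidal behaviour and a change of treatment are discontinuation criteria, and receiving a prohibited treatment is a removal criterion. Participants with such events may have no later scores. An all-AE table keeps the event whether or not later visits take place.

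**The case against.** The strongest reply is that one loosely used word is being given a technical meaning. The English is informal throughout, the term is undefined, and the same section says that security outcomes, which are defined through AEs, will be analysed in everyone treated. The authors may simply mean adverse events. This stands: a reader might infer that a related-only subset is intended, and the protocol does not establish it. The sentence still needs correcting, because it fixes the compared quantity with a term that does not match the outcome.

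A reader might also infer that causality is judged with knowledge of the arm, because therapists count as researchers, are not listed as blinded, and researchers sign the records. The protocol does not say so. No judge is named, and the word covers blinded assessors as well. An article may leave that detail to the full protocol, so its absence is not itself the fault. Unblinded judgement is a possible risk only.

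Nor does the text support saying that worsening depression or self-harm would go unanalysed. The scale scores cover them in part, and a data monitoring committee reviews the data.

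Finally, 80% versus 20% attribution is an extreme assumption. Even a split of 8/30 against 2/30, which it would give if 10 of 30 in each arm had an event, has a two-sided Fisher p of about 0.08. This is fair, and is why a range including equal attribution is shown. The pilot's stated thresholds for proceeding also rest on completion and drop-out, not on the AE test.

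**Conclusion.** The point holds as a mismatch between the safety outcome and its analysis. All AEs are collected, and the only stated between-arm test is for an undefined term that usually means related events. On the literal reading, the comparison rests on a relatedness judgement whose maker and blinding are unstated, and it could drop serious psychiatric events judged unrelated.

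The size is conditional. It is nil if the authors mean all AEs, and there is no excess of false positives if attribution is equal between arms. Otherwise false positives are roughly 4–54% over the assumed range, against 2–3% for all AEs. These figures rest on assumed event risks and attribution rates and show direction and scale only.

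Severity is minor to moderate. The trial is a small pilot, but its participants are minors, safety is among its stated aims, and its results are meant to inform a larger trial.

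**What to change.** In Statistical analysis, replace the adverse reaction term with all AEs and all SAEs from the first session to week 12, regardless of relatedness, in everyone treated at least once, described and compared by arm. Show events judged related as a secondary table.

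The cost is a change of wording, one extra table and somewhat higher headline event counts. No new data are needed, since Security outcomes already requires AEs to be recorded through follow-up.

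Giving the relatedness judgement to the blinded outcome assessors is not recommended. Reviewing bleeding, bruising or pain at needle sites could reveal which needle was used and unmask the people rating the CDRS-R. Once the main comparison no longer depends on relatedness, that step is not needed to protect it.
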